### Immunogenicity endpoints and analysis

Immunogenicity evaluation will be conducted as follows:

Evaluation of bAB antibody responses specific for wild-type SARS-CoV-2—GMT of serum anti-S.FL, anti-S1, and anti-RBD bAB at Visit 1 (baseline) and Visit 4 (30 days after Visit 1).Evaluation of nAB antibody responses specific for wild-type SARS-CoV-2—GMT of serum anti-S nAB at Visit 1 (baseline) and Visit 4 (30 days after Visit 1).Evaluation of the bAB and nAB ratio for wild-type SARS-CoV-2—the ratio of bAB and nAB titers directed against the investigational pDNA vaccine at Visit 1 (baseline) and Visit 4 (30 days after Visit 1).Evaluation of the fold rise in bAB responses for wild-type SARS-CoV-2—GMFR and proportion of participants with a 4-fold increase in serum anti-S.FL, anti-S1, and anti-RBD binding antibody titers at Visit 1 (baseline) and Visit 4 (30 days after Visit 1).Evaluation of cellular immune responses (CD3, CD4, CD8, CD45RA, CCR7, IFN-γ, IL-2, IL-4, IL-13, and TNF) at Visit 1 (baseline) and Visit 4 (30 days after Visit 1).

#### Binding antibody evaluation

Values below the detection limit (1:50).Antibody measurements will be logarithmically calculated (log 10)

#### Neutralizing antibody evaluation

Values below the detection limit (1:20)Antibody measurement will be logarithmically calculated (log 10)

### Exploratory immunogenicity endpoints and analysis (exploratory analysis)

Evaluation of bAB antibody responses for SARS-CoV-2 variants of concern—GMT of serum anti-S bAB at Visit 1 (baseline) and Visit 4 (30 days after Visit 1).Evaluation of nAB antibody responses for SARS-CoV-2 variants of concern—GMT of the serum anti-S nAB at Visit 1 (baseline) and Visit 4 (30 days after Visit 1).Evaluation of the bAB and nAB ratio for SARS-CoV-2 variants of concern—the ratio of bAB and nAB titers directed against the investigational pDNA vaccine at Visit 1 (baseline) and Visit 4 (30 days after Visit 1).

### Interim analysis {21}

An interim analysis of immunogenicity and safety data will be conducted after completion of safety and immunogenicity assays for all the samples through Visit 4. The analysis will include safety data for all subjects at each visit until Visit 4. Interim immunogenicity analysis will include immunogenicity data from all subjects at Visit 1 and Visit 4. This interim data will be used to evaluate the optimal dosage for use in future clinical trials.

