## Abstract

**Background:**

SARS-CoV-2 has been responsible for a worldwide public health crisis and a pandemic that began in February 2020, with approximately 679 million cases and over 6.7 million deaths to date. Despite the existence of approved COVID-19 vaccines, these vaccines are either based on mRNA technology or viral vectors. Imam Abdulrahman Bin Faisal University (IAU) has developed a thermally stable plasmid DNA (pDNA)-based vaccine candidate using a platform approach that enables the rapid development of vaccines against emerging viral diseases. The pDNA vaccine developed by IAU encodes the full-length, optimized version of the SARS-CoV-2 Spike protein. Key advantages of this pDNA vaccine are that it is cost-effective, thermally stable, and can be used to administer multiple immunizations without incurring anti-vector responses, making it a promising candidate as a vaccine booster dose.

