### Trial Design {8}

This investigational vaccine study is a Phase 1, randomized, dose-finding, single-center study, enrolling healthy adults. In total, 42 healthy individuals will be enrolled in the study. The eligible individuals will be randomized to receive either the investigational vaccine or placebo (Saline). Subjects will be enrolled at a 1:1:1 ratio in a dose-escalating manner to one of three cohorts (Cohort 1: low dose level, “1 mg”; Cohort 2: mid-dose level, “2 mg”; Cohort 3: high-dose level, “4 mg”). All subjects will receive a single dose of the vaccine or placebo IM.

The study duration for an individual subject is approximately 7 months. Interim analysis for safety will be performed on the data that are collected from all study subjects at Visit 1, Visit 2 (1 day after Visit 1), Visit 3 (7 days after Visit 1), and Visit 4, while interim analysis for immunogenicity will be performed on the data that are collected from all study subjects at Visit 1 and Visit 4. Table 3 illustrates the schedule of activities (SOA) and timing of study visits and assessments.

**Table 3 T3:** Schedule of study visits and assessments—Visit 1 to Visit 5.

Visit number	Screening	1	2	3	4	5	Unplanned	Unplanned
Visit description	Screening	Vax 1	Next-Day Follow-up Visit (Vax 1)	1-Week Follow-up Visit (Vax 1)	1-Month Follow-up Visit	6-Month Follow-up Visit	Potential COVID-19 Illness Visit	Potential COVID-19 Convalescent Visit
Visit window (Days)	0 to 28 Days Before Visit 1	Day 1	1 to 3 Days After Visit 1	6 to 8 Days After Visit 1	28 to 35 Days After Visit 1	154 to 168 Days After Visit 1	Optimally Within 3 Days After Potential COVID-19 Illness Onset	28 to 35 Days After Potential COVID-19 Illness Visit
Physical examination (height, weight, BMI, vital signs, general appearance, examination of skin, auscultation of the heart, auscultation of the lungs, palpation of the abdomen, examination of extremities)	X	X	X	X	X	X		
ECG	X			X				
Collect blood sample for hematology and chemistry^a^	~13.5 ml	~13.5ml	~13.5 ml	~13.5 ml	~13.5 ml	~13.5 ml		
Collect screening blood sample for HIV, HBsAg, HBc Ab, and HCV Ab tests	X included in chemistry sample							
Perform alcohol test	X							
Perform drug panel test	X							
Perform serum pregnancy test (if appropriate)	X							
Perform urine pregnancy test (if appropriate)		X				X		
Urinalysis^a^	X	X				X		
Obtain nasal swab (mid-turbinate) for COVID-19	X	X^b^					X	
Collect non-study vaccine information	X	X	X	X	X	X		

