### Immunogenicity assessment

#### Humoral immune response

Approximately 4 ml of whole blood will be taken during Visit 1, Visit 4, and Visit 5. The blood must be drawn prior to vaccination of the subjects. The serum should be separated from the whole blood prior to conducting humoral antibody response assessments.

The humoral immune response will be evaluated as follows:

Binding antibody responses to the S.FL, S1, and RBD S1 of wild-type SARS-CoV-2 using ELISA.Binding antibody response to the S.FL of SARS-CoV-2 variants of concern using V-plex COVID-19 panel.Neutralizing antibody directed against wild-type SARS-CoV-2 using V-plex assay COVID-19 (ACE2) neutralizing assay kit.Neutralizing antibody directed against SARS-CoV-2 variants of concern using V-plex COVID-19 panel.

Antibody response to the spike protein of SARS-CoV-2 will be evaluated for all subjects by measurement of the bAB and nAB responses as follows:

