#### Cellular immunity assessment

Cellular immunity will be evaluated in all recruited subjects. Approximately 16 ml of blood will be taken from each subject during Visit 1, Visit 4, and Visit 5. The blood should be drawn prior to vaccination of the subjects. Peripheral blood mononuclear cells (PBMCs) will be collected for the assessment of cell-mediated immunity using intracellular cytokines staining.

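### A SARS-CoV-2 infection between Visit 1 and Visit 4 would count as an antibody response to vaccine or placebo, and an asymptomatic one could not be identified

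*Protocol article*

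**What the plan says.** **Who is analysed.** Interim analysis {21} states: "Interim immunogenicity analysis will include immunogenicity data from all subjects at Visit 1 and Visit 4". Trial Design {8} describes the interim immunogenicity data in the same inclusive way. Neither section mentions infection after dosing.

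**What the result is for.** Interim analysis {21} continues: "This interim data will be used to evaluate the optimal dosage for use in future clinical trials".

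**What is measured.** The Abstract describes the product: "The pDNA vaccine developed by IAU encodes the full-length, optimized version of the SARS-CoV-2 Spike protein". The section Humoral immune response lists, for wild type, "Binding antibody responses to the S.FL, S1, and RBD S1 of wild-type SARS-CoV-2 using ELISA" and, for variants, "Binding antibody response to the S.FL of SARS-CoV-2 variants of concern using V-plex COVID-19 panel". Immunogenicity endpoints and analysis, and its exploratory counterpart, describe neutralizing antibody as anti-spike. No serology against a non-spike antigen is named. For cellular immunity the protocol says only: "Peripheral blood mononuclear cells (PBMCs) will be collected for the assessment of cell-mediated immunity using intracellular cytokines staining". The stimulating antigen is not given.

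**How infection is detected.** In Table 3 the row "Obtain nasal swab (mid-turbinate) for COVID-19" is marked at Screening, at Visit 1 (swabs taken 1 to 2 days before) and at the unplanned illness visit. It is not marked at Visits 2 to 5. Infection status is monitored, but it is listed with the safety assessments and is not linked to the immunogenicity analysis.

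**The concern.** Visit 4 falls 28 to 35 days after dosing, and the protocol itself provides illness and convalescent visits, so it expects that some participants may be infected. Infection and vaccination both present spike. An antibody rise at Visit 4 in someone infected in between therefore cannot be attributed to one or the other from the named antibody assays.

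With groups this small, one person can move a geometric mean. In a dose group, an infection looks like immunogenicity and could favour that dose. In placebo, it shrinks or reverses the contrast. The protocol describes the platform as one of relatively low immunogenicity in humans (Background and rationale {6a}; Table 1), so the true effect may be small enough to be imitated or hidden. Cohorts are dosed in sequence, at least 12 to 14 days apart, so a change in circulating virus during the trial would also fall unequally on the dose levels.

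**Working it through.** **Inputs from the protocol**
- Three cohorts of 14: 3 × 14 = 42, which agrees with the stated total.
- Allocation 3:1 within a cohort. Since 14 × 0.75 = 10.5, the ratio cannot be exact. Randomization {16} assigns the first two subjects of a cohort one to each arm. If the other 12 split 9 to 3, a cohort has 1 + 9 = 10 vaccine and 1 + 3 = 4 placebo, so 3 × 4 = 12 pooled placebo. I use 10, 4 and 12.
- The protocol states no power calculation, infection rate, titer rise or SD, so there is no such figure to reproduce.

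**Assumptions (not in the protocol)**
- Risk *p* of infection between Visit 1 and Visit 4: 3%, range 1% to 5%.
- Extra titer rise *f* caused by an infection: 10-fold, range 5 to 20.
- SD of log10 fold rise: 0.3, range 0.2 to 0.4.

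**Chance of at least one infection, 1 − (1 − p)^n**

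| Group | p = 1% | p = 3% | p = 5% |
|---|---|---|---|
| One dose group, n = 10 | 10% | 26% | 40% |
| One cohort's placebo, n = 4 | 4% | 11% | 19% |
| All subjects, n = 42 | 34% | 72% | 88% |

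For example, 1 − 0.97^10 = 1 − 0.737 = 0.263.

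**Effect of one infected subject on a group's GMFR, f^(1/n)**

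| Group | f = 5 | f = 10 | f = 20 |
|---|---|---|---|
| Dose group, n = 10 | 1.17 | 1.26 | 1.35 |
| Pooled placebo, n = 12 | 1.14 | 1.21 | 1.28 |
| One cohort's placebo, n = 4 | 1.50 | 1.78 | 2.11 |

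If a dose group has 11 subjects, the 10-fold figure is 1.23 instead of 1.26.

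**Effect on the proportion with a 4-fold rise.** One infected subject who would otherwise not respond adds 1/10 = 10 percentage points in a dose group and 1/4 = 25 points in one cohort's placebo.

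**Comparison of two equally immunogenic doses, 10 subjects each**
- Shift in the difference: log10(10)/10 = 0.10.
- Standard error: 0.3 × √(2/10) = 0.134.
- Ratio: 0.10/0.134 = 0.75 standard errors (1.12 at SD 0.2; 0.56 at SD 0.4).

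**Vaccine against placebo.** Suppose the true GMFR ratio is 1.5 and one placebo subject has a 10-fold rise. The observed ratio is 1.5/1.78 = 0.84 against one cohort's 4 placebo subjects, or 1.5/1.21 = 1.24 against 12 pooled.

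**What an analysis rule could and could not repair.** A symptomatic infection should be swabbed, and its result would be on file. An asymptomatic one is neither swabbed nor distinguishable by anti-spike serology. No wording in a statistical analysis plan can remove a case that was never measured.

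**The case against.** **The analysis set may be defined elsewhere.** The phrase about all subjects sits in a paragraph on the timing and content of the interim. It may mean only that all cohorts are included. Evaluable sets and the handling of intercurrent events commonly go to the statistical analysis plan, which is not shown. This stands in part. A reader might infer that the protocol deliberately keeps confirmed infections in the analysis. It does not say so, and the lack of an exclusion rule would not by itself be a finding. What remains is that the text as written is inclusive, and that the visit schedule leaves asymptomatic infection undetectable whatever the analysis plan says.

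**Safeguards exist.** A negative swab is required shortly before dosing, people in high-exposure workplaces are excluded, and non-study vaccines other than influenza are not allowed. The first does not reach past dosing, and the second lowers the risk without removing it. The third does mean that outside COVID-19 vaccination is already addressed and needs no new rule here.

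**Not every immunogenicity assay is shown to be spike-based.** Correct. "Antibody response to the spike protein of SARS-CoV-2 will be evaluated for all subjects by measurement of the bAB and nAB responses" settles it for antibodies, but the antigen for the cellular assay is unnamed. A reader might extend the point to the T-cell results; the protocol does not support that without knowing the antigen.

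**Randomization and blinding make infection mainly noise, and excluding infected subjects can introduce selection.** Both are fair. Three or four placebo subjects per cohort give little balance, but setting people aside for a post-randomization event is not neutral either, so neither analysis should stand alone.

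**The size is assumed and can be overstated.** This stands. Late infections may not have raised titers by Visit 4, and symptomatic cases would be swabbed, so the chances above overstate the undetectable part.

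**Conclusion.** The concern holds in a limited form. With the inclusive wording, the spike-directed antibody assays and swabs only on illness, an infection between Visits 1 and 4 enters GMT, GMFR and 4-fold rise as a response, and an asymptomatic one cannot be found.

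The size is moderate and conditional. At an assumed 3% risk, a given 10-subject dose group has about a 26% chance of at least one infection (10% to 40% for risks of 1% to 5%). One 10-fold rise then multiplies its GMFR by 1.26, about 0.75 standard errors in a comparison of two doses at an assumed log10 SD of 0.3.

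Two stronger conclusions might be drawn and are not supported. The 72% chance applies to any of the 42 subjects, not to a particular dose group. Nor can it be said that dose choice would be overturned: the shift is under one standard error in the central case, safety data are considered too, and the protocol states no threshold or automatic dose-selection rule. The point merits a change to the plan but does not undermine the trial.

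**What to change.** **Analysis.** For GMT, GMFR, 4-fold rise and the dosage evaluation, pre-specify an analysis that leaves out Visit 4 data from subjects with evidence of SARS-CoV-2 infection between Visits 1 and 4. Report it beside the all-subjects analysis. Apply the same rule to the cellular results if the stimulating antigen is spike, and state which antigen is used.

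**Definition of infection.** Use the swab results from illness visits, plus anti-nucleocapsid antibody on the serum already drawn at Visits 1 and 4. The vaccine insert is spike, so a new nucleocapsid response points to infection. The exclusion criteria bar only current COVID-19, so some participants may already be nucleocapsid-positive at Visit 1 and cannot seroconvert. For them, pre-specify the rise that counts as reinfection.

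**Cost.** About 42 × 2 = 84 extra assays, with no extra visit or blood draw. Serum volume must be confirmed first, because only about 4 ml of whole blood per visit is allotted to all humoral assays. The infection-free set may lose a subject or two, and it conditions on a post-randomization event, which is why both analyses should be shown.

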## Oversight and monitoring

### Composition of data monitoring committee {5d}

A DMC by Icon plc will be implemented for this Phase 1 COVID-19 vaccine trial for the purpose of reviewing the safety data of participants during their periodic visits. The role of the DMC is to review safety data as described in the DMC charter. Escalation between doses will be based on DMC review. Dose escalation will start at least 12–14 days after the previous cohort received the study vaccine for (Cohort 1 and Cohort 2) and (Cohort 2 and Cohort 3).

### Adverse events reporting and harm {22}

All AEs, SAEs, and Serious Adverse Reactions (SARs) will be monitored in each participant after the administration of the investigational vaccine. All SAEs and AEs should be documented in the eCRF as well as the AE and SAE forms. In addition, any medications and therapeutics used should be reported in the eCRF. The investigator must notify the sponsor and the DMC of AEs and SAEs. The investigator will immediately notify the sponsor (within 24 h) of any SAE to comply with any ethical and/or legal obligations toward the study participants and to ensure that all stopping/halting rules are met. The sponsor will inform the DMC. If any halting rules are to be applied, vaccination of the subjects must be stopped until a full review of safety data by the DMC and health authorities has been performed. For all subjects who experience a SAE, follow-up information deemed as significantly new by the investigator will be reported no later than 24 h after they have been made aware, and follow-up information deemed as not significantly new by the investigator will be reported no later than the next business day after they have been made aware.

#### Stopping rules

The stopping rules will be applied based on AEs, SAEs, clinical laboratory assessments, and diary card data. These data will be monitored by the investigator and sponsor for the purpose of identifying possible risk.

The following are considered as stopping/pausing rules in this Phase 1 study:

A participant receiving the investigational vaccine (in any cohort) who develops Grade 4 AEs or laboratory abnormalities that are assessed by the investigator as possibly related to the vaccine with no other alternative or plausible causes. Vaccination will be stopped until a full safety review is completed.Two or more participants receiving the investigational vaccine (in any cohort) who develop Grade 3 AEs or laboratory abnormalities after vaccination that are assessed by the investigator as possibly related to the vaccine with no other alternative or plausible causes. Vaccination will be stopped until a full safety review is completed.A participant receiving the investigational vaccine (in any cohort) develops a fever (>40°C) for more than 24 h after receiving the vaccine with no other alternative or plausible causes. Vaccination will be stopped until a full safety review is completed.If a participant in any cohort requires admission to an intensive care unit (ICU) for COVID−19 infection after receiving the investigational vaccine that is assessed as possibly related to the vaccine with no other plausible or attributable causes. Vaccination will be stopped until a full safety review is completed.A participant receiving the investigational vaccine (in any cohort) who develops a SAE that is assessed by the investigator as possibly related to the vaccine with no other alternative or plausible causes. Vaccination will be stopped until a full safety review is completed.A participant receiving the investigational vaccine (in any cohort) who develops a serious adverse reaction that is assessed by the investigator as possibly related to the vaccine with no other alternative or plausible causes. Vaccination will be stopped until a full safety review is completed.Two or more participants receiving the investigational vaccine (in the same cohort) who develop severe non-serious adverse reactions, whether or not they are within the same organ class.If a participant in any cohort dies and this is aassessed by the investigator as possibly related to the investigational vaccine. In this case, all vaccination will be halted.

### Frequency and plan for inspecting trial conduct {23}

Quality assurance (QA) includes all the planned and systematic actions that are established to ensure that the clinical study is performed, and the data are generated, documented (recorded), and reported according to ICH GCP and local/regional regulatory standards. An inspection from the Sponsor or qualified designee, who is independent of and separated from routine monitoring, may periodically arrange inspections/audits of the clinical study by reviewing the data obtained and procedural aspects. These inspections may include on-site inspections/audits and source data checks. Direct access to source documents is required for the purpose of these periodic inspections/audits. This study will be conducted in compliance with ICH CGP guidelines. This study will also be conducted in accordance with the most recent version of the Declaration of Helsinki. Records and documents, including signed ICFs, pertaining to the conduct of this study must be retained by the Investigator for 25 years after study completion unless local regulations or institutional policies require a longer retention period. No records may be destroyed during the retention period without the written approval from the Sponsor. No records may be transferred to another location or party without written notification of the Sponsor.

### Plans for communicating important protocol amendments to relevant parties (e.g., trial participants, ethical committees) {25}

Study procedures will not be changed without the mutual agreement of the PI and the sponsor. If there are any changes to the study protocol, these changes will be documented in a study protocol amendment. If a protocol amendment requires a change to the ICF, the IRB Comitee must approve the revised ICF before it is used.

### Dissemination plans {31a}

Upon study completion, results will be published in a peer-reviewed medical scientific journal. Interim results may be released by the sponsor.

## Discussion

Current approved Covid-19 vaccines primarily utilize either mRNA technology or recombinant protein-based approaches. While highly effective in pandemic responses, each platform has distinct limitations. As single stranded molecule highly susceptible to enzymatic degradation, mRNA requires further sophisticated encapsulation with lipid nanoparticles for protection and efficient cellular delivery. Furthermore, this fragility necessitates an ultra cold chain shipment and storage (-70 °C) to prevent degradation. Conversely, protein based vaccines are generally more and easier to store but primarily induce humoral (antibody) responses. They are notably less efficient at activating cytotoxic T cells, which are crucial for destroying virus infected cells. In contrast, pDNA based vaccine platform offer unique and advantageous profile that addresses many of the issues. pDNA is stable, double stranded, circular molecule that can be store at refrigerated temperature or even with ambient temperature, which greatly reduce the costs associated with cold chain logistics. Once delivered into host cell, pDNA activates both arms of adaptive immune systems; the humoral and cellular responses. Furthermore, the pDNA vaccine include selfaduvinating activity that provoke innate immune responses (12.13). This balanced immune activation makes pDNA a promising platform for future vaccine strategies. As such, IAU has developed a thermally stable pDNA-based vaccine candidate using a platform approach that enables the rapid development of vaccines against emerging viral diseases, including SARS-CoV-2. The pDNA vaccine developed by IAU is a synthetic, codon-optimized sequence encoding either the full-length Spike (S.opt.FL) as genes of interest. Potential key advantages of this pDNA vaccine include that it is cost-effective, thermally stable, and can be used for multiple rounds of immunization without the limitations of anti-vector responses, making it an appealing choice as a booster dose. Given concern surrounding the continuous emergence of new COVID-19 variant strains that evade the immunity gained from previous rounds of vaccination, it will be essential to implement a vaccine platform that can be quickly adapted to newly emergent strains and on a regular/seasonal basis. The manufacturing of pDNA vaccines is robust, scalable, and highly adaptable. Moreover, pDNA manufacturing is conducted through a series of quick manufacturing steps, offering a unique advantage compared to the manufacturing of protein vaccines and even mRNA vaccines.

The IAU COVID-19 pDNA vaccine is formulated without the need for encapsulation using nanoparticles or the use of adjuvants. In addition, the codon-optimized S gene is inserted into the pVax1 plasmid backbone that is FDA-approved for clinical trials and has been tested in numerous preclinical and clinical studies. Importantly, unlike with the previously developed Covid-19 pDNA vaccines, the IAU pDNA is admistred without the application of physical delivery methods. In our previous preclinical studies, we demonstrated that the administration of S.opt.FL pDNA induces high levels of S-specific bAB and nAB against SARS-CoV-2. Notably, the pDNA vaccination predominantly elicited Th1-mediated immune responses, characterized by S-specific IgG2 and IFN-γ production. This Th1-skewed immune profile is essential in conferring protection against virus challenge (22, 23).

This study aims to investigate the safety, tolerability, and immunogenicity of this prophylactic vaccine against COVID-19 when administered as a booster heterologous vaccine in participants already receiving mRNA vaccine using a single ascending dose design. Previous clinical trial on Coronavirus pDNA vaccine found that increasing the doses to 6 mg did not yield superior immunogenicity, supporting the use of lower doses (28). Saline was selected as a control to provide a strictly inert baseline, ensuring a clear assessment of the vaccine's overall clinical impact in accordance with the internationally accepted safety standards. The study will offer valuable insight regarding the safety and immunogenicity of this pDNA vaccine as a booster vaccine in participants who have previously received a COVID-19 mRNA vaccine. In addition, this study will determine the safest maximum tolerated dose in participants receiving this pDNA vaccine. The study will also provide information regarding the humoral and cellular immune responses elicited by the vaccine and their durability in pDNA vaccine recipients. Lastly, as with other RNA viruses, it will be essential to explore the cross-protection of this SARS-CoV-2 vaccine against antigenically divergent strains (29–35), and this study will evaluate these effects through its exploratory objective. All of this data will be critical to determine which cohort to inform subsequent clinical trials.
